**Table 1. Maternal and Neonatal Risk Factors for EOS in the Dutch guidelines**

| Maternal risk factors                                                                                                                                                                                          | Neonatal risk factors                                                                              |
|----------------------------------------------------------------------------------------------------------------------------------------------------------------------------------------------------------------|----------------------------------------------------------------------------------------------------|
| Red flags                                                                                                                                                                                               |                                                                                                    |
| Parenteral antibiotic treatment given to the woman for confirmed or suspected invasive bacterial infection (such as septicemia) at any time during labor, or in the 24-hour periods before and after the birth | Respiratory distress starting more than 4 hours after birth                                        |
| Suspected or confirmed infection in another neonate in case of a multiple pregnancy                                                                                                                            | Neonatal epileptic seizures                                                                        |
|                                                                                                                                                                                                                | Need for mechanical ventilation in a term neonate                                                  |
|                                                                                                                                                                                                                | Signs of shock                                                                                     |
| Non-red flags                                                                                                                                                                                           |                                                                                                    |
| Invasive group B streptococcal infection in a previous neonate                                                                                                                                                 | Altered behavior, -responsiveness or -muscle tone                                                  |
| Maternal group B streptococcal colonization, bacteriuria or infection in the current pregnancy                                                                                                                 | Feeding difficulties (feed refusal, gastric retention, vomiting, distended abdomen)                |
| Suspected or confirmed rupture of membranes without contractions for more than 24 hours in a term birth                                                                                                        | Apnea and bradycardia                                                                              |
| Preterm birth following spontaneous labor (before 37 weeks' gestation)                                                                                                                                         | Signs of respiratory distress (tachypnea, moaning, retractions, nasal flaring)                     |
| Suspected or confirmed rupture of membranes for more than 18 hours in a preterm birth                                                                                                                          | Hypoxia (for example, central cyanosis or reduced oxygen saturation level)                         |
| Intrapartum fever higher than 38°C or suspected or confirmed chorioamnionitis                                                                                                                                  | Neonatal encephalopathy                                                                            |
|                                                                                                                                                                                                                | Need for cardio-pulmonary resuscitation                                                            |
|                                                                                                                                                                                                                | Need for mechanical ventilation in a preterm neonate                                               |
|                                                                                                                                                                                                                | Persistent pulmonary hypertension                                                                  |
|                                                                                                                                                                                                                | Temperature abnormality (lower than 36°C or higher than 38°C) unexplained by environmental factors |
|                                                                                                                                                                                                                | Local signs of infection (for example, affecting the skin or eyes)                                 |

**Intervention EOS calculator:** Using the EOS calculator application, between 0-24 hours after birth, maternal EOS risk factors combined with the results of physical examination of the newborn are used to assign a risk category and accompanying clinical recommendation based on estimated EOS incidence (low: <0.65; intermediate: 0.65-1.54; high:> 1.54 per 1000 live newborns) for each newborn at-risk for an infection. The EOS calculator results are used to guide a clinical management decision on performing either a diagnostic work-up and start of empiric intravenous antibiotics for (suspected) EOS, or a conservative approach with routine

controls of vital parameters (heart rate, respiratory rate, and temperature every 3 hours) by the nurse. In case of routine controls, re-evaluation of physical appearance by a pediatric resident or pediatrician will take place within 24 hours postpartum. As an additional safety precaution in our study, the newborns will be observed for 24 hours using vital parameters. In case antibiotics are started, the need for further treatment is assessed after 24-36 hours of treatment depending on blood culture results, infection parameters, and clinical condition of the newborn. Discontinuation of antibiotics and discharge is at the discretion of the treating physician.

## 4. STUDY POPULATION

### 4.1 Population (base)

Newborns are eligible for participation if they have a postmenstrual age of 34 weeks or more, are 0-24 hours old, and in case at least one EOS risk factor or clinical sign of infection (suspected of EOS) is present within the first 24 hours of life.

Ten centers will include patients (five randomized to NVK guideline, five to EOS calculator use). Each center is supposed to include around 183 patients. Per center there are between 1500 and 2500 live births a year. The number of eligible patients is estimated to be between 300/year (center with 1500 live births/year and 20% suspected EOS) and 500/year (2500 live births/year and 20% suspected EOS). With an average number of patients of 2000 per center, a baseline suspected EOS of 20%, and at least 50% participation rate of eligible patients, the average number of patients per center that can participate in a one-year period is:  $2000 \times 0.2 \times 0.5 \times 1 = 200$  patients. This is more than enough for the needed 183 per center during an 18-month inclusion period. In the Netherlands there are currently no competing trials in this patient population.

### 4.2 Inclusion criteria

In order to be eligible to participate in this study, a subject must meet all of the following criteria:

- postmenstrual age of 34 weeks or more;
- age between 0-24 hours;
- at least one EOS risk factor or clinical sign of infection (suspected of EOS) present within the first 24 hours of life (Table 1);
- parental/guardian consent.

### 4.3 Exclusion criteria

A potential subject who meets any of the following criteria will be excluded from participation in this study:

- major congenital anomalies;
- language barrier (lack of effective communication or whenever it hinders understanding).

### 4.4 Sample size calculation

Superiority: In the control group we expect 40% antibiotic therapy in newborns at risk for EOS. To reduce this to 25% (reduction 15%) by use of the EOS calculator, (80% power, ICC 0,0025, alpha 0,05, 10 hospitals) a total sample size of 330 is required.

Non-inferiority: In the control group and the intervention group, we expect that 10% of newborn infants will fulfill one of the predefined safety criteria. The non-inferiority margin

is set at 15% (absolute difference 5%). The required sample size is 1640 (per cluster 164) (80% power, ICC 0,0025, alpha 0,025, 10 hospitals). Because both hypotheses regarding superiority (reduction in antibiotic therapy) and non-inferiority (adverse clinical outcome) have to be met, the study sample size equals the largest of the two sample sizes.

The potential drop-out or withdrawal is estimated at 10%. We will include 2x 915 newborn infants (total=1830), which means 183 per cluster. The analyses will be performed both according to the intention-to-treat (ITT) principle and according to a per-protocol (PP) analysis. All participants taking part in the study will be analyzed according to the ITT principle. Protocol deviations will be recorded and participants in whom major protocol deviations have occurred will be excluded from the PP analysis. These analyses will be both performed, since attending physicians are able to opt for clinical management not according to the advice of the assigned study protocol. This will be registered as a protocol violation in the eCRF, with accompanying justification (see chapter 3).

## 5. INVESTIGATIONAL PRODUCT

### 5.1 Name and description of investigational product

For this study the EOS calculator was developed as a smartphone application (by everywhereIM, [name]). For additional information, we refer to the attached documents:

- Technical Documentation EOS calculator;
- Productsheet EOS calculator;
- Post-market surveillance plan;
- VWS CE certificering;
- EU declaration of conformity.

The clinical investigation plan equals this study protocol outlined in this document. There is no detailed user manual because the smartphone application is completely self-explanatory. Below is a short description of its procedure:

1. Sign up using work-affiliated email-address, confirm using confirmation mail;
2. Enter input data for a newborn;
3. Press 'Show results';  
The app then displays:
  - the *a priori* EOS risk at birth;
  - the EOS risk for each scenario of clinical status of the newborn with accompanying recommendation regarding medical management;
4. Press 'Back' if you want to check or change your inserted data, or
5. Press 'Save and send': all inserted data and the recommendation will be sent to your linked email address. During the study, these data will also be sent to the email address of the research nurse. These data will contain a unique identifier for that particular calculation session (not traceable to the newborn), for quality control and monitoring purposes.

These emails are study documents and will be saved for the duration of 15 years after the end of the research period, as is common for all research documents. They will be stored at Tergooi Hospital, the sponsor. All inputted data will be coded and stored at the server of everywhereIM as well. This is not traceable information and will not be accessible for third parties. EverywhereIM is ISO- and NEN-certified.

The CE marking and classification of the EOS Calculator app are valid for five years, and was granted in accordance with the Medical Device Directive 93/42/EEG and the system of

GHTF/SG1/N15: 2006 Principles of Medical Devices Classification respectively (see 'VWS CE certificering' and 'Technical Documentation EOS Calculator' part 2.3). The validity of these documents has been verified at the secretariat of the Medical Research Ethics Committee of the Amsterdam UMC, location Academic Medical Center (on July 20, 2021). All other documents provided are in accordance with article 82 of the Medical Device Regulation.

## **5.2 Summary of findings from non-clinical studies**

The development and validation of two linked predictive models for EOS was described in two clinical papers (14,15), and recently summarized (29). Briefly, these models employ a Bayesian approach. The first model established newborn's probability of EOS entirely based on the maternal risk factor, or EOS risk at birth (15). EOS risk at birth is calculated using gestational age and maternal variables that are available at the moment of birth. The relationship of each variable to the outcome was analyzed separately and then combined into a multivariate model. The second predictive model for EOS that was developed quantifies how the baseline risk is modified by the newborns clinical examination (14). Three clinical-presentation categories (clinical illness, equivocal, and well appearing) were defined and calculated likelihood ratios for each. Newborns will be stratified based on both their clinical presentation and the three levels of sepsis at birth. And management choices are suggested (no treatment-observation-treat empirically with antibiotics). This all was developed into a Web-based EOS calculator that provides physicians with an explicit risk estimate. The first release was in December 2012.

The process of the web-based EOS calculator has been copied into the app. Validation has been performed to ensure that the app functions properly. More detailed information about technical specifications and the validation of the smartphone application is included in the above mentioned documents (see 'Technical Documentation EOS Calculator' chapter 2 and 7).

## **5.3 Summary of findings from clinical studies**

The EOS calculator has been developed and validated on data of over >600,000 newborns born at  $\geq 34$  weeks' gestation. The implementation study then included 204,485 newborns and showed a decrease in antibiotic use from 5.0% to 2.6% (16). EOS incidence and readmissions for EOS did not change after implementation. The EOS calculator has now been evaluated in more than 20 studies, of which 8 with actual implementation. Meta-analysis shows up to an average of 44% less antibiotic use, without indications of negative

consequences (17). Implementation in Tergooi hospital gave a similar result and a Dutch multicenter study shows a similar potential (18). There are no known implementation studies in which the use of the EOS calculator was not effective or proved unsafe. Since the content of the smartphone application is an exact copy of the web-based version, the content has already been validated in America. This study will validate the content for the Dutch population.

#### **5.4 Summary of known and potential risks and benefits**

**Benefit:** Meta-analysis shows up to an average of 44% less antibiotic use, without indications of negative consequences (17).

**Risk:** We like to address that the use of the EOS calculator is not able to capture all newborns with a proven EOS, comparable to any other guideline. It is important to realize that missed cases does not mean that the missed cases have died or have a worse outcome. It means that antibiotics were not started immediately after birth. The EOS calculator-based strategy is therefore not automatically inadequate or less safe, but it indicates that the calculator relies to a greater extent on clinical observation for 24 hours that is advised by the calculator. Achten et al. reviewed all cases of EOS in a meta-analysis. Among before-after implementation studies, they found 5 of 18 (28%) “missed” cases in cohorts with EOS calculator-based management, compared to 8 of 28 “missed” cases (29%) in cohorts with conventional management strategies. All newborns with “missed” EOS were eventually started on antibiotics. To have no missed cases, we must treat all babies after delivery, which is undesirable because we know that antibiotics early in life do harm.

## 6. METHODS

### 6.1 Study parameters/endpoints

#### 6.1.1 Main study parameter/endpoint

**Co-primary superiority outcome:** The proportion of patients that started antibiotic therapy for suspected and, or proven EOS in the first 24 hours after birth.

**Co-primary non-inferiority outcome:** A composite non-inferiority outcome regarding the presence of one or more of the following four predefined safety criteria, namely 1) the need for any respiratory support, and/or 2) the need for an intravascular fluid bolus for hemodynamic instability due to sepsis, and/or 3) referral to a Neonatal Intensive Care Unit for sepsis treatment, and/or 4) proven EOS.

- Respiratory support is defined as any form of respiratory support (invasive ventilation, continuous positive airway pressure (CPAP), high flow nasal cannula (HFNC), low flow oxygen) during the first week of life.
- Intravascular fluid bolus is defined as the intravenous administration of a fluid bolus of 10ml/kg within 15-30 minutes. It is the first step in the treatment of hemodynamically unstable newborns due to sepsis.
- Proven EOS is defined as a blood or cerebrospinal fluid (CSF) culture obtained within 72 hours after birth growing a pathogenic bacterial species.

The mentioned co-primary outcome criteria overlap with non EOS causes. For example, prematurity is also associated with the need for respiratory support or asphyxia with the need for intravascular fluid administration. It is for this that a randomization trial was chosen. We do not expect that a reduction in antibiotic exposure by using the EOS calculator will lead to significantly more of these outcomes. Because the trial is not blinded, there is a change that (unconscious) bias may occur. We expect that this will be limited by the cluster-randomized design on the one hand, and by the relatively objective criteria, on the other hand.

Furthermore, we decided for a composite non-inferiority outcome, based on four predefined criteria, since the incidence of each individual criterion is very low.

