### 7.2.2 Serious adverse events (SAEs)

A serious adverse event is any untoward medical occurrence or effect that

- results in death;
- is life threatening (at the time of the event);
  - o except, if it concerns neonatal (advanced) life support directly after birth;
  - o except if it concerns surfactant therapy;
  - o except referral to a NICU:
    - (need for mechanical ventilation because of) surfactant therapy;
    - insertion of central venous lines;
    - respiratory support for prematurity.
- requires hospitalization or prolongation of existing inpatients' hospitalization;
  - o unless a newborn will start with antibiotic therapy for (suspected) EOS during the observation period or after discharge, but within 72 hours after birth. See also 5.4.;
  - o unless it is due to prematurity.
- results in persistent or significant disability or incapacity; or
- any other important medical event that did not result in any of the outcomes listed above due to medical or surgical intervention but could have been based upon appropriate judgement by the investigator.

Referral to a NICU will be included in the electronic Case Report Form (eCRF), since this is one of the non-inferiority criteria.

Each study site will report all SAEs to the coordinating investigators within 24 hours after becoming aware of the event. The coordinating investigators will report all SAEs to the sponsor without undue delay after obtaining knowledge of the events. The sponsor will report the SAEs through the web portal *ToetsingOnline* to the accredited METC that approved the protocol, within 7 days of first knowledge for SAEs that result in death or are life threatening followed by a period of a maximum of 8 days to complete the initial preliminary report. All other SAEs will be reported within 15 days after the sponsor has first knowledge of the serious adverse events.

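### The safety composite counts respiratory support that began before the allocated protocol could act, which pulls the relative risk towards 1 and so favours non-inferiority

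*Protocol*

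**What the plan says.** Section 6.1.1 makes the co-primary safety outcome a composite of four criteria. The first two read: "1) the need for any respiratory support, and/or 2) the need for an intravascular fluid bolus for hemodynamic instability due to sepsis". The fluid bolus and the intensive care referral are tied to sepsis. Respiratory support is not.

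The definition that follows is broad: "Respiratory support is defined as any form of respiratory support". Its list of forms runs from invasive ventilation down to "low flow oxygen) during the first week of life". No start point is set relative to the treatment decision.

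Section 4.2 admits a newborn on a single Table 1 item. Table 1 lists "Need for mechanical ventilation in a term neonate" among the red flags and "Need for mechanical ventilation in a preterm neonate" among the non-red flags. Respiratory distress and hypoxia are also entry signs.

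Section 3 (Equality) places clinical evaluation within 4 hours of birth and has the advice of the allocated protocol followed only once eligibility is established.

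Section 6.1.1 concedes overlap with causes other than early-onset sepsis (EOS), for example that "prematurity is also associated with the need for respiratory support", and gives this as the reason for randomising. Section 8.1 declares non-inferiority if the upper 95% limit of the relative risk is no higher than 1.5, against an expected 10% in the control group.

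**The concern.** Support that began before the first protocol-guided assessment cannot result from either strategy. Where ventilation was the entry sign, the outcome is present at enrolment. These events occur at the same expected rate in both arms and carry no information about the calculator.

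Randomisation answers a different question: it makes such events balanced on average, so they do not bias a risk difference. It does not stop them inflating numerator and denominator of a ratio alike. In a superiority comparison that dilution is conservative. Here it works in favour of the claim being tested.

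Section 1 justifies the trial partly because no study has examined the effect of treatment delay under the calculator. Events that precede the decision cannot bear on delay.

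**Working it through.** **Inputs.** Section 4.4: 10% composite rate in both arms, 5-point margin (10% to 15%), one-sided alpha taken as 0.025, 80% power, intracluster correlation (ICC) 0.0025, 10 hospitals, 164 per cluster, 1640 in total before drop-out (820 per arm). Section 8.1: relative-risk limit 1.5. The share f of control-arm events that the allocation cannot affect is not in the documents and is an assumption throughout.

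**1. The plan's own figure.** Individually randomised, per arm: 2 × 0.10 × 0.90 × (1.960 + 0.842)² / 0.05² = 565.1, so 566. Design effect: 1 + 163 × 0.0025 = 1.4075. Total: 2 × 566 × 1.4075 = 1593, which is 2.8% below 1640. Power at 1640 is 81.2%. The figure reproduces closely, on the absolute-difference scale.

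**2. Can f be read from the documents?** Only the proven-EOS component can be bounded. At most 2 per 1000 live births (Summary), with 20% of births suspected (section 4.1), gives 0.002 / 0.20 = 1% of participants, if every case is eligible and participation is unrelated to EOS. How the rest of the 10% divides between components, and when support started, is not stated. So f has to be shown as a range.

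**3. Dilution.** Let R be the true relative risk on the events that the allocation can affect. Newborns with a fixed event are counted once and are equally common in both arms. Then

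composite RR = f + (1 − f) × R.

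Setting this to 1.5 gives the largest R that leaves the composite at the limit: R = (1.5 − f) / (1 − f).

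- f = 25%: 1.25 / 0.75 = 1.67
- f = 50%: 1.00 / 0.50 = 2.0
- f = 80%: 0.70 / 0.20 = 3.5

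**4. Chance of declaring non-inferiority.** Normal approximation on log RR, with p₀ = 0.10, p₁ = 0.10 × [f + (1 − f)R] and

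SE² = 1.4075 × [(1 − p₀)/(820 p₀) + (1 − p₁)/(820 p₁)],

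probability = Φ[(ln 1.5 − ln composite RR)/SE − 1.96].

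Example, f = 50%, R = 1.5: p₁ = 0.125, composite RR 1.25, SE = √[1.4075 × (0.01098 + 0.00854)] = 0.166, probability = Φ(0.1823/0.166 − 1.96) = Φ(−0.86) = 19.5%.

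| f (assumed) | R that puts the composite RR at 1.5 | P(non-inferior) if R = 1.5 | P(non-inferior) if R = 2 |
|---|---|---|---|
| 0 | 1.50 | 2.5% | <0.1% |
| 25% | 1.67 | 7.7% | 0.2% |
| 50% | 2.0 | 19.5% | 2.5% |
| 80% | 3.5 | 44.1% | 26.5% |

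**5. Absolute scale.** The difference in composite rates is 0.10 × (1 − f) × (R − 1), which is exactly the difference in the events that can be affected. It is not diluted. At the limit, f = 50% means 5% to 10% and f = 80% means 2% to 7%: both +5 points.

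**6. Power of a composite restricted to post-assessment events.** Same formula with R = 1, 820 per arm and the limit 1.5: about 64% at a 10% rate, 35% at 5% and 17% at 2%.

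**The case against.** The strongest reply is that the protocol discloses the overlap, chose a broad composite because each criterion is rare, and set a 5-point absolute margin in section 4.4. Fixed events leave a 5-point difference untouched, and section 8.1 ties the 1.5 limit to a 15% rate. This stands as a description of the absolute scale. It does not rescue the decision rule, which is written on the relative risk.

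Second, a start-time rule adds judgement in an open-label trial, where section 6.1.1 relies on fairly objective criteria, and it costs events. Both are fair, and they argue against replacing the primary composite. They do not argue against recording times and reporting a second version.

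Three stronger readings are tempting and are not supported:

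- A reader might infer that most composite events are settled before either protocol acts. No section gives that share. The hospitals provide care up to Level II, so newborns ventilated at entry may be few, and respiratory distress and hypoxia are signs and not support. At f = 25% the effect is modest.
- A reader might set the serious adverse event text, "except, if it concerns neonatal (advanced) life support directly after birth", against the endpoint as a contradiction. That text governs which events are reported as serious. A reporting filter need not match an endpoint definition.
- A reader might infer that arms will differ in gestational age because randomisation is unstratified and the model unadjusted. The protocol is silent on both, and a statistical analysis plan may settle them. Chance imbalance could also go either way.

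**Conclusion.** The point holds in a limited form. As written, section 6.1.1 counts events that the allocation cannot cause, including ventilation that was the entry sign. Under the rule in section 8.1 those events move the composite relative risk towards 1 and make non-inferiority easier to declare. Randomisation does not remove this.

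The direction follows from the text. The size depends on f, which is unknown: over an assumed range of 25% to 80%, a true 1.5-fold rise in the events that matter passes in about 8% to 44% of trials instead of 2.5%. The calculation assumes equal fixed-event rates in the two arms, a 10% control rate and the planned ICC. Support that starts or escalates after the assessment is informative, so only part of the component is inert.

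**What to change.** Add to the eCRF the start time and any escalation time of respiratory support, and the time of the first protocol-guided assessment. Section 6.3 describes daily recording during admission (in the paragraph on newborns given antibiotics). Daily entries could not separate support before and after the assessment on day 1.

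Prespecify a second composite that counts respiratory support only if it starts or escalates after that assessment, and that leaves out support that was itself the entry criterion. The other three criteria stay as they are. Report it beside the all-support composite, and state that it will be weighed when non-inferiority is interpreted. Define escalation in advance, to limit judgement by unblinded staff.

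The cost is a few eCRF fields and an analysis with fewer events. At about 35% power (5% rate) or 17% (2% rate) on the 1.5 scale, it should be read by its estimate and confidence interval. Making it a second test that must be passed would usually fail a safe strategy. Making it the primary endpoint would require the expected rate, margin and sample size to be derived again.
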